### Assignment of interventions: blinding

#### Who will be blinded *{17a}*

This is a non-blinded randomised control trial by virtue of there being one interventional group compared with TAU.

#### Procedure for unblinding if needed *{17b}*

As this is a non-blinded study, an unblinding process will not be necessary.

### Data collection and management

#### Plans for assessment and collection of outcomes *{18a}*

There will be three data-collection time points. Data will be collected via the case record form and self-report questionnaires at baseline (t0), at post-6-week intervention (t1) and at 12-week follow-up (t2). This will be performed entirely by the research assistant. For details of primary and secondary outcome measures, see the ‘Outcomes {12}’ section.

#### Plans to promote participant retention and complete follow-up *{18b}*

During the screening process, study candidates will receive information about the study in the form of a study ‘ad’ and an extensive participant information leaflet describing the study in detail. Study candidates will have ample opportunity to ask questions about the study, at all stages of participation. Eligible candidates will be encouraged to enrol only if they are willing and able to commit to the 18-week study period (6-week intervention plus 12-week follow-up). Every effort will be made by the research assistant to remain in contact, as deemed appropriate, with all study participants throughout their participation. Participants will also have the contact details of the research team should they wish to make contact outside of other study contact points.

#### Data management *{19}*

All data will be recorded on a study-specific case report form (CRF) that has the patient’s unique study identifier code on each page. Study investigators will enter the data from CRFs into a designed study-specific REDCap database that is log-in restricted to formally approved research team members only. Data will be entered primarily by the project’s research assistant (CF) and verified by a different study investigator (SL/DL) to mitigate any risk of data entry errors (e.g. incorrect or duplicate data).

The data collected and all the research-related documents (hard copy CRF, questionnaires and electronic study key) will be stored securely in a locked office in the principal investigator’s office at the Mater Misericordiae University Hospital (MMUH). Only the principal investigator and the co-investigators can have access to these documents. The records will be kept for 5 years following study closure or until such time that study outcomes are fully disseminated. All electronic files will be encrypted and accessed via password-protected computers.

The electronic REDCap database also allows for specified ranges and automatic calculations to reduce entry errors. The study REDCap database will have automatic calculations for study questionnaires and specified ranges entered for each questionnaire response to ensure accurate data entry. Data will be cleaned by investigators upon completion of data collection to ensure good quality data.

#### Confidentiality *{27}*

All the data collected will remain coded and confidential. A unique subject number will be provided to each individual patient participating in the study. The front page of the CRF which will be labelled with the study code number and select patient information will be stored separately to the remainder of the CRF, in the form of an electronic, password-protected study key, containing select data about the participant (such as study code, patient name and DOB) to ensure data is re-identifiable. Only study investigators will have access to the data as CRF forms will be stored in a locked office of the hospital Psycho-Oncology service that only study investigators have access to. CRFs will be retained for the duration of the research project to ensure corresponding REDcap data can be checked and verified.

#### Plans for collection, laboratory evaluation and storage of biological specimens for genetic or molecular analysis in this trial/future use *{33}*

This is not applicable as no biological samples will be collected.

### Statistical methods

#### Statistical methods for primary and secondary outcomes *{20a}*

Outcome analyses will be performed by a dedicated biostatistician. An intention-to-treat analysis will be performed on all randomised patients and a per-protocol analysis will be performed on all patients who complete the study. Descriptive statistics will be calculated for all outcome measures at each time point. Continuous variables will be reported using means, medians, standard deviations and score ranges. Categorical variables will be described using frequencies and percentages.

Descriptive and inferential statistics will be obtained using the appropriate statistical methods that seek to address our identified objectives. The primary analysis will compare the effect of the interventions on the primary outcome; distress levels at 12 weeks post-completion of the intervention period (i.e. c18 weeks post-baseline). All outcome analyses will be conducted according to an intention-to-treat principle, i.e. all randomised participants will be included in the main analysis and will be analysed as randomised, regardless of protocol adherence. Secondary analysis will include the analysis of the primary outcome post-intervention and analysis of the secondary and treatment process outcomes detailed previously post-intervention and at the 12-week follow-up. Linear mixed models on the outcome measures over time will be fitted to evaluate the effect of both study conditions, which intrinsically adjusts for baseline scores.

Statistical significance will be assessed from a *p* value < 0.05 from the group by time interaction term. For all tests, two-sided *p* values will be used, which will be reported to four decimal places with *p* values < 0.001 reported as *p* < 0.001. The Bonferroni method will be used to appropriately adjust the overall level of significance for multiple secondary outcomes as applicable. In the case of a significant result, planned contrasts of the group effects at the post-treatment period and at the 12-week follow-up will be used to investigate the direction and pattern of effects and outlined in advance in the SAP. As a key component of the reporting of the analyses of outcomes, the mean changes (irrespective of statistical significance) and correlations of the measures between the assessment time periods will be obtained. SPSS will be used to conduct the analyses.

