**Discussion:**

To our knowledge, this protocol describes the first RCT which directly examines the effect of a group-based psychological intervention on Irish patients experiencing cancer recurrence in the context of COVID-19. The outcome of this trial is likely to be twofold: It will determine if the psychological intervention achieves its primary objective of distress amelioration 3 months post-intervention and to establish the feasibility of delivering this intervention in a virtual format.

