#### Intervention group: compassion-focussed therapy and breathing pattern retraining

The CFT and BPR intervention will be delivered in a group format and will last approximately 90 min per group session. Group sessions will each comprise two segments, one being CFT and the other being BPR. The CFT will seek to emphasise concepts such as practising compassion, fostering self-awareness, self-soothing, mindfulness exercises, reducing self-criticism and practising kindness and inner warmth. The BPR segments will seek to introduce and develop breath work that can aid self-soothing, relaxation and bodily activation. The physicality of the breath work is largely performed by the treating psychologist (SL) but is also assisted by a senior physiotherapist from the Mater hospital by way of training videos that participants can view and use for practice. Further details of each individual session and its content are provided in Table 1.

**Table 1 Tab1:** Layout of the 6-week compassion-focussed therapy and breathing pattern retraining intervention

Session	Summary of sessions
1	Part 1: Breathing pattern retraining education, breathing assessment, simple breath work. Physiotherapy demo in video and simple breath work Part 2: Understanding compassion, CFT explained, model and intervention review; why we need compassion, our tricky brains and defining emotions such as shame, fear and loneliness; Monkey Mind meditation, just noticing our busy minds
2	Part 1: Motivation and our complex brains; understanding motives and emotions—breaking through fear and blocks Part 2: How our thoughts and images affect our minds and brains; breathing patterns—the mind–body connection. Breathing pattern retraining education—exploring the physiotherapy-led exercises
3	Part 1: Compassionate thinking; the 3 components of self-compassion: mindfulness, common humanity and kindness. How this links with soothing breathing Part 2: Dysfunctional breathing and stress; breathing awareness and breathing practices such as tender self-compassion break and affectionate breathing
4	Part 1: Compassionate mind training through imagery—creating your compassionate self Part 2: Creating your compassionate self; breathing pattern retraining techniques and practice combining compassionate imagery

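### The per-protocol set is defined by completing the study, not by receiving the programme, so it is a completer analysis and should not be reported as the effect in those treated

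*Protocol article*

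**What the plan says.** All references are to the protocol article.

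- **Analysis sets, section {20a}.** Besides an intention-to-treat analysis of all randomised patients, "a per-protocol analysis will be performed on all patients who complete the study". The same section then says "All outcome analyses will be conducted according to an intention-to-treat principle", and that "all randomised participants will be included in the main analysis and will be analysed as randomised, regardless of protocol adherence".
- **Process outcomes, section {20a}.** Secondary analysis is to include "analysis of the secondary and treatment process outcomes detailed previously post-intervention and at the 12-week follow-up". Neither the Outcomes section {12} nor Table 2 describes any treatment process outcome.
- **Non-adherence, section {20c}.** The heading covers protocol non-adherence. The text deals only with missing data.
- **Study period, section {18b}.** Candidates should be "willing and able to commit to the 18-week study period (6-week intervention plus 12-week follow-up").
- **Programme.** It has six weekly sessions (Table 1) and "will be delivered in a group format and will last approximately 90 min per group session". Controls are offered it only after the 18-week study period.
- **Data listed.** Section {18a} names a case record form and self-report questionnaires at t0, t1 and t2. Table 2 lists the five instruments and demographics. Session attendance appears in neither.
- **Feasibility.** The Discussion part of the abstract gives as a second expected result "to establish the feasibility of delivering this intervention in a virtual format". Feasibility is not among the objectives {7} or outcomes {12}.

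**The concern.** Readers take a per-protocol analysis to describe patients who received the treatment as planned. Here membership depends on staying in the study. The two can come apart in either direction: a patient may skip sessions and still return questionnaires, or attend every session and then miss follow-up.

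There are two consequences. First, the contrast in this set mixes those who received the programme with those who did not, so it does not answer the adherence question that its label implies. Second, study completion happens after randomisation and may be related to both arm and outcome. Section {22} allows participants who find the interventions distressing to be removed from the trial. During the 18 weeks only one arm receives that intervention, so removals for this reason fall on one arm. If those patients count as non-completers and fare worse than average, the comparison shifts in favour of the programme.

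The adherence question also needs a measure of sessions received, and the article lists none. The phrase about process outcomes, which might have supplied one, points to nothing in the text.

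**Working it through.** **1. The plan's own figure.** Inputs from section {14}: difference 1 unit, SD 2, two-sided alpha 0.05 (sidedness from {20a}), power 80%.

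- Normal approximation: n = 2 × (1.96 + 0.842)² × (2/1)² ≈ 62.8, so 63 per group.
- Exact two-sample t-test: 63.8, so 64 per group.
- With 20% attrition: 64 / 0.80 = 80 per group.

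The stated 64 and 80 reproduce. The point below does not touch them.

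**2. Who is in the set under the stated rule.** The rule covers all patients in both arms. Controls have no programme during the study, so the only criterion that both arms can meet is completing follow-up.

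| Patient | Received programme | In the set as written |
|---|---|---|
| Intervention, attends, completes follow-up | yes | yes |
| Intervention, few or no sessions, completes follow-up | no | yes |
| Intervention, attends, lost to follow-up | yes | no |
| Control, completes follow-up | not applicable | yes |
| Control, lost to follow-up | not applicable | no |

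The second and third rows show that membership does not track receipt.

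**3. How many are excluded.** At the planned attrition, 0.20 × 160 = 32 patients leave the set because of a post-randomisation event. The documents do not say how these would divide between arms, so no size or direction can be given for the resulting bias.

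**4. Dilution, illustration only.** The share c of intervention-arm completers who received the programme is an assumption, because the documents give none. Assume also a full 1-unit effect with receipt, no effect without it, SD 2 and 64 completers per arm. Then contrast = c × 1.0, and power comes from the two-sample t-test.

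| c | Contrast (DT units) | Power |
|---|---|---|
| 1.0 | 1.0 | 80% |
| 0.9 | 0.9 | 71% |
| 0.8 | 0.8 | 61% |
| 0.7 | 0.7 | 50% |
| 0.5 | 0.5 | 29% |

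The contrast column only restates the assumed share. It shows that the set does not estimate the effect of receipt. It does not predict what this trial will see.

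**5. What a randomisation-based estimate does instead.** Controls cannot take up the programme during the study, so the complier-average effect is the intention-to-treat difference divided by the share of the intervention arm reaching the pre-specified attendance level. Under the same assumptions, with 80% of all patients randomised to the intervention reaching it, the difference is 0.8 and 0.8 / 0.8 = 1.0. This keeps both arms as randomised.

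**6. Internal consistency of {20a}.** A per-protocol analysis and a sentence placing every outcome analysis under intention-to-treat cannot both hold literally. The likely intent is that the main analyses follow intention-to-treat, but the text does not say so.

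**The case against.** **Completion may imply treatment.** Section {18b} describes the study period as including the 6-week intervention, so a patient who attended no sessions has arguably not completed the study. This shows that the wording is ambiguous. It does not supply a criterion: no number of sessions is given, and the rule also applies to controls, who have none to attend.

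**Requiring the endpoint is normal.** Many per-protocol sets require the primary assessment, so excluding attenders without it is not a fault in itself. That stands. The fault is that completion is the only requirement.

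**A reader might infer that attendance is not collected.** The article does not support that. It lists no attendance measure, but it condenses a fuller protocol, and neither the case record form nor the analysis plan is shown.

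**A reader might also infer that feasibility cannot be assessed.** That is not supported either. Section {11c} has the research assistant record eligible candidates and those who do not proceed because of ineligibility, non-consent or withdrawal, and completion at t1 and t2 will be observed. What lacks a listed measure is uptake of the online sessions.

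**The dilution figures are assumed.** They are. Zero effect without attendance is itself doubtful, since participants also have training videos to practise with.

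**An attendance threshold would select too.** It would, and on one side only, because controls have no sessions. This is why the fix rests on a randomisation-based estimate.

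**Conclusion.** The point holds in a limited form. As written, the per-protocol set is a completer set under the wrong label. Its result should not be read as the effect in those treated, because membership does not depend on receipt and the selection may differ by arm. Two textual faults sit beside it: the conflict within {20a} over intention-to-treat, and the reference to process outcomes that the article does not detail.

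The consequence is confined to a supplementary analysis. The main intention-to-treat estimate, its p value and the sample size are unaffected. The size of any distortion cannot be derived from the documents: 0.9, 0.8 and 0.7 at 10, 20 and 30% non-attendance are illustrations, and the selection bias is unquantified. The change is worth making because it is cheap and prevents a secondary result from being misread.

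**What to change.** - Call the analysis of patients who complete the study a completer analysis.
- List attendance at each of the six online sessions as a recorded variable, or state that the case record form already holds it.
- Make the adherence analysis a complier-average effect with randomisation as the instrument and an attendance level fixed before the data are seen. State its assumption that allocation does not affect outcome in those below that level; the training videos and partial attendance both bear on this.
- Keep any attendance-defined per-protocol set as supportive only, because the control arm has no sessions to which a threshold could apply.
- Reword the all-outcomes intention-to-treat sentence so that it covers the main analyses and allows these supplementary ones.
- Replace the reference to process outcomes with a named measure. Session attendance can serve both as this and as the missing uptake component of feasibility, alongside recruitment, consent, withdrawal and retention.

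**Cost:** six attendance fields, one added analysis and some rewording, with no new visits or staff. The article reports 8.5% of patients recruited, so at that stage attendance could still be logged prospectively for most participants.

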### Trial design *{8}*

The COMFORT trial is designed as a prospective, randomised, controlled, single-centre superiority trial with two parallel groups and a primary endpoint of psychological distress 18 weeks post-enrolment. The study will randomise patients who have experienced a cancer recurrence since March 2020 into two groups on a 1:1 basis: one that receives compassion-focussed therapy and radical breathing retraining and the other control group who receives TAU. As all patients will be endorsing elevated levels of distress, it is possible that they will be indicated for individual psychosocial care, as part of the hospital’s psycho-oncology service (CNS, Social Work, Psychology & Psychiatry), but this is likely to be controlled for across both groups. Figure 1 illustrates the study design, timelines of the intervention and baseline as well as follow-up evaluations. The estimated duration for the main investigational plan (e.g. from the start of screening of the first participant to the last participant processed and finishing the study) is 15–18 months.

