### Sample size *{14}*

Sample size was estimated using a target power of 80%, at a type I error rate of 0.05, and was calculated relative to the primary outcome measure; distress rating on the 11-point Distress Thermometer (DT) scale. The statistical test assumed was an independent samples *t*-test for group differences in the change from baseline to subsequent assessment, assuming that the randomisation ensures no systematic baseline or other covariate group differences. The minimal clinically significant difference for the DT is estimated to be 1 unit (standard deviation of improvement of 2 units), similar to other 11-point Likert scale questionnaires [30]. Calculation produced a suggested sample size of 64 per group. Allowing for a potential attrition rate of 20%, our final sample size is 80 participants per group (8 groups of 10).

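### The mixed model tested by group-by-time does not by itself adjust for baseline; as usually fitted it compares mean change, which forgoes precision although it stays valid

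*Protocol article*

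**What the plan says.** Statistical methods for primary and secondary outcomes {20a} puts the primary comparison at 12 weeks after the intervention, about 18 weeks after baseline. Linear mixed models on the outcomes over time "will be fitted to evaluate the effect of both study conditions, which intrinsically adjusts for baseline scores". Significance is read from the group-by-time interaction. Contrasts at the two follow-up times come only after a significant result, and their details are left to the SAP.

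Plans for assessment and collection of outcomes {18a} gives three times: baseline (t0), after the 6-week intervention (t1) and 12-week follow-up (t2).

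Sample size {14} is based on an "independent samples *t*-test for group differences in the change from baseline to subsequent assessment". The planning values are "The minimal clinically significant difference for the DT is estimated to be 1 unit (standard deviation of improvement of 2 units".

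**The concern.** The protocol credits the model with a property that depends on how it is set up. A mixed model adjusts for baseline if baseline is a covariate, or if baseline is an outcome and the arms share one mean there. Section {20a} mentions neither. Testing a group-by-time interaction suggests that baseline sits among the outcomes. With the arm means free at that visit, the t2 interaction is a difference in mean change.

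A change score subtracts the whole of any baseline difference between arms. Conditioning on baseline subtracts only the part that predicts follow-up. The change-score comparison is therefore never more precise in large samples, and in a given trial it responds more to a chance imbalance whenever the slope of follow-up on baseline is below 1. An analyst who takes the sentence at its word has no reason to add the covariate or the constraint. The same sentence governs the primary outcome and the four secondary scales.

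**Working it through.** **Inputs from the protocol.** Difference 1 DT unit, SD of change 2, power 80%, alpha 0.05 (Sample size {14}); two-sided tests ({20a}); 1:1 allocation (Trial design {8}). **Assumed, because the protocol gives no planning value:** the correlation rho between DT at t0 and t2, and the SDs s0 and s1 at those visits.

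**1. The plan's own figure.** A two-sample t-test with difference 1 and SD 2 (noncentral t) needs 64 per group, with power 0.801. Allowing for 20% attrition, 64/0.8 = 80. Both stated figures reproduce.

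**2. What the interaction estimates.** Take three visits, 64 per arm, complete data and an exchangeable correlation, with free arm means at t0. The generalised least-squares variance of the t2 interaction is 0.125. The change-score variance is 2 × 4/64 = 0.125, the same. In one simulated data set (rho 0.5) the random-intercept model gave −1.0313, the difference in mean change was −1.0313, and analysis of covariance (ANCOVA) gave −1.0576. The unconstrained model reproduces the change score, not the baseline-adjusted estimate.

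**3. The same model with a common t0 mean.** Its variance is 0.081, 0.094 and 0.106 at rho 0.3, 0.5 and 0.7, exactly the ANCOVA values. The adjustment comes from the constraint.

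**4. Size of the forgone precision.**

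- Var(change) = s0² + s1² − 2·rho·s0·s1
- Var(adjusted) = s1²(1 − rho²)
- Difference = (s0 − rho·s1)², never negative

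*Equal SDs, SD of change 2.* Here 2s²(1 − rho) = 4, so the adjusted variance is 4(1 + rho)/2.

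| rho | adjusted variance (against 4) | saving | power at 64 per arm (against 0.80) |
|---|---|---|---|
| 0.3 | 2.6 | 35% | 0.94 |
| 0.5 | 3.0 | 25% | 0.90 |
| 0.7 | 3.4 | 15% | 0.86 |

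*Baseline SD 1.6, as an example of narrowing by the DT ≥ 4 entry cut; SD of change still 2.* Solving 4 = 1.6² + s1² − 2·rho·1.6·s1 for s1:

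| rho | s1 | (1.6 − rho·s1)² | saving (divided by 4) | power at 64 per arm |
|---|---|---|---|---|
| 0.3 | 1.77 | 1.14 | 28.5% | 0.91 |
| 0.5 | 2.24 | 0.23 | 6% | 0.82 |
| 0.7 | 2.76 | 0.11 | 3% | 0.81 |

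**5. Chance imbalance.** The change-score and adjusted estimates differ by (1 − slope) × the baseline difference between arms. With SD 2 at both visits and rho 0.5 the slope is 0.5. At 64 per arm the standard error of the baseline difference is 2 × √(2/64) = 0.35. An imbalance of one standard error shifts the change-score estimate by 0.5 × 0.35 = 0.18 units relative to the adjusted one, against a target of 1 unit.

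**The case against.** **The premise of free baseline means is not written down.** This is true. {20a} does not say whether the arm means at t0 are free or common. With a common mean the model has ANCOVA precision and the sentence would be correct. Parameterisation often sits in the SAP, which is not shown. So the finding is conditional. It still stands, because {20a} asserts the property outright and hands only the contrasts to the SAP, and because the adjustment would come from an added constraint and not from the mixed model as such. The change-score sizing in {14} points towards the unconstrained reading without proving it.

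**No planned power is lost.** This stands. A reader might infer that the trial is underpowered, but the sample size already assumes a change score with SD 2 and reproduces. The loss is relative to a better analysis, not to the plan.

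**The estimate is not biased.** This also stands. A reader might infer a validity failure, but under randomisation the change contrast is unbiased. It is shifted only conditionally on a chance imbalance.

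**The DT ≥ 4 entry cut does not make matters worse.** It is tempting to argue that selecting on high distress makes the over-correction severe. It does not. Average regression to the mean affects both arms alike and cancels in the contrast. Under a linear relation the cut leaves the slope unchanged, and by narrowing the baseline spread it shrinks both chance imbalances and the variance penalty. In a normal model with assumed mean 5 and SD 2.3 before the cut, the saving falls from 35%, 25% and 15% to about 20%, 14% and 8% at rho 0.3, 0.5 and 0.7.

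**Conclusion.** The concern holds as a wrong or at best incomplete statement about the primary model. A linear mixed model over t0, t1 and t2 tested by group-by-time does not adjust for baseline unless a covariate or a constraint is added, and the protocol names neither. The consequence is forgone precision and avoidable sensitivity to chance imbalance, not bias and not a shortfall against the planned 80% power.

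The variance saving runs from about 3% to 35% over the scenarios examined. The larger figures need equal SDs at baseline and follow-up, and the entry cut makes the smaller ones more plausible. All of them rest on assumed correlations and SDs. The change is worth making because it costs almost nothing and adjustment does not lose precision in large samples.

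**What to change.** In {20a}, and in the SAP, replace the clause on intrinsic adjustment with an explicit specification, either:

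- DT at t1 and t2 as outcomes, with baseline DT, baseline-by-time and arm-by-time terms; or
- DT at t0, t1 and t2 as outcomes, with the arms constrained to a common mean at t0.

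Name the t2 arm contrast from that model as the primary estimate. Use the same form for PHQ-9, GAD-7, IES-R and Mini-MAC. The constrained form also keeps participants with only a baseline score in the model, which suits the protocol's commitment to include everyone randomised.

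The cost is protocol and SAP wording. Table 2 shows that every scale is already collected at baseline, and the sample size need not change. Trial status reports 8.5% of patients recruited and {21b} plans no interim analysis, so on the status reported the change can be fixed before any comparison of outcomes by arm.

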#### Secondary outcomes

Secondary outcomes of the study include levels of depressed mood, levels of anxiety, traumatic distress and reported mental adjustment to cancer. These will be measured using the following questionnaires:The Patient Health Questionnaire (PHQ-9) total score [time frame: 3 months post-group programme]oThe PHQ-9 is a clinically validated, nine-item instrument for screening, monitoring and evaluating symptoms of depression [24]. It incorporates the Diagnostic and Statistics Manual for Mental Disorders, fourth edition (DSM-IV), diagnostic criteria into a brief self-report tool and asks how often a person has ‘been bothered’ by any of the itemised problems in the preceding 2 weeks. Scores range from 0 to 27 and scores ≥ 10 had a sensitivity of 88% and a specificity of 88% for major depression. Scores of 5, 10, 15 and 20 represent mild, moderate, moderately severe and severe depression, respectively.The Generalised Anxiety Disorder Questionnaire (GAD-7) score [time frame: 3 months post-group programme]oThe GAD-7 is an easy-to-use, self-administered screening instrument comprising seven questions. Scores range from 0 to 21, with scores ≥ 10 achieving a sensitivity of 89% and a specificity of 82% for generalised anxiety [Spitzer et al., 2006]. It also enjoys modest effectiveness at screening for other anxiety disorders [25]. Scores of 5, 10 and 15 are the cut-off thresholds for mild, moderate and severe anxiety, respectively.The Impact of Event Scale-Revised (IES-R) score [time frame: 3 months post-group programme]oThe IES-R is a 22-item self-report measure that assesses subjective distress caused by traumatic events [26]. Items correspond to 14 of the 17 DSM-IV symptoms of post-traumatic stress disorder (PTSD). Respondents are asked to name a specific traumatic event with subsequent answers reflecting how distressed or bothered they have felt by each item listed, over the previous 7 days. The instrument yields a score ranging from 0 to 88 along with subscale scores that relate to intrusive phenomena, avoidance and hyperarousal. A cut-off score of ≥ 34 has been suggested for the IER-R as a threshold for probable PTSD, as it has been found to provide good values on sensitivity (86–89%) and specificity (80–81%) in two samples of survivors of war [27].The Mini-Mental Adjustment to Cancer Scale (mini-MAC) score [time frame: 3 months post-group programme]oThe Mini-MAC is a 29-item self-rating questionnaire which was designed to provide a method of assessing specific responses to cancer along the following dimensions: ‘fighting spirit’, ‘helpless/hopeless’, ‘anxious preoccupation’, ‘fatalism’ and ‘avoidance’ [28]. There are published clinical cut-off scores for the dimensions of Summary Negative Adjustment (SNA) and Summary Positive Adjustment (SPA) when scores on thesis scales exceed 36 or fall below 47, respectively [29].

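### Plain Bonferroni for the secondary outcomes is valid, but Holm's step-down procedure gives the same error control and never less power

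*Protocol article*

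**What the plan says.** Under Statistical methods for primary and secondary outcomes {20a}, the protocol article judges significance by a p "value < 0.05 from the group by time interaction term" of a linear mixed model. The tests are two-sided. For multiplicity it says: "The Bonferroni method will be used to appropriately adjust the overall level of significance for multiple secondary outcomes as applicable". If a result is significant, planned contrasts at the end of treatment and at the 12-week follow-up are to follow, and these are left to the SAP.

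The outcomes concerned are under Outcomes {12}: "Secondary outcomes of the study include levels of depressed mood, levels of anxiety, traumatic distress and reported mental adjustment to cancer". They are measured by the PHQ-9, GAD-7, IES-R and mini-MAC. Objectives {7} makes improvement on these measures the secondary objective.

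The trial is sized on the Distress Thermometer alone (Sample size {14}): "Sample size was estimated using a target power of 80%, at a type I error rate of 0.05".

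**The concern.** The article names a particular multiplicity method, so the choice was not left to the SAP and can be judged here. Bonferroni tests each of m outcomes at 0.05/m, whatever the other outcomes show. Holm's procedure starts at the same threshold and relaxes it after each rejection. It needs no further assumption, and in terms of which hypotheses are rejected it can only do as well or better.

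At stake is power on the stated secondary objective. The sample size gives about 80% power for one test at 0.05. A secondary outcome with the same standardised effect, tested at a Bonferroni level, has clearly less. Holm recovers part of that loss when several measures truly improve, which is the result the secondary objective looks for.

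**Working it through.** **Inputs from the protocol article.** Two-sided alpha 0.05; 64 evaluable per group, 80 after 20% attrition; Distress Thermometer difference 1 unit with SD 2, a standardised effect of 1/2 = 0.5; four secondary instruments.

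**Assumptions, not in the article.** Standardised effects on the secondary outcomes of 0.5 or 0.3 SD, on all or only some of the outcomes; equal correlation between test statistics of 0, 0.5 or 0.7; a family of m = 4, with m = 8 as a sensitivity case (four instruments at two time points).

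**Step 1: the plan's own figure.** By the normal approximation, n = 2 × (1.96 + 0.8416)² × 2² / 1² = 62.8, so 63 per group. The exact two-sample t-test gives 63.77, so 64 per group with power 80.1%. Then 64 / (1 − 0.20) = 80. The stated 64 and 80 reproduce.

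**Step 2: thresholds for m = 4.** Bonferroni tests every p value at 0.05/4 = 0.0125. Holm orders the p values and tests them at 0.05/4 = 0.0125, 0.05/3 = 0.0167, 0.05/2 = 0.025 and 0.05/1 = 0.05, stopping at the first failure. No Holm threshold is below 0.0125. A p value under 0.0125 always passes, because every smaller p value passes too. Holm therefore rejects all that Bonferroni rejects, whatever the effects or correlations.

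**Step 3: Bonferroni power by formula.** The mean of the test statistic is 0.5 × √(64/2) = 2.828.
- m = 4: the critical value at 0.0125 is 2.498, so power is Φ(2.828 − 2.498) = 63%.
- m = 8: at 0.05/8 = 0.00625, power is 54%.

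**Step 4: Holm against Bonferroni by simulation.** Correlated z statistics, 64 per arm, 200,000 replicates per scenario. Ranges run over the three correlations.

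| Scenario | Bonferroni, average power per real outcome | Holm |
|---|---|---|
| m = 4, all effects 0.5 SD | 63% | 71–74% |
| m = 4, two of four effects 0.5 SD | 63% | 65–66% |
| m = 4, one of four effects 0.5 SD | 63% | 63% |
| m = 4, all effects 0.3 SD | 21% | 24–26% |
| m = 8, all effects 0.5 SD | 54% | 64–66% |

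With all four effects at 0.5 SD, the chance that all four are significant is 16% against 40% at correlation 0, 33% against 54% at 0.5, and 40% against 60% at 0.7. The chance of at least one rejection is the same for both methods (89.1% at correlation 0.5). No replicate had a Bonferroni rejection that Holm missed.

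**Step 5: error control.** With no real effects (m = 4), familywise error is identical for the two methods: 4.9%, 4.3% and 3.8% at correlations 0, 0.5 and 0.7. With two or three of four effects real, Holm stays at or below 3.9%.

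**The case against.** The strongest reply is that nothing here is wrong. Bonferroni is valid, prespecified and simple, and no other section contradicts it. That stands, and it limits the point to an optional improvement.

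It can also be said that the headline gain is near best case. An effect of 0.5 SD on every secondary outcome is borrowed from the Distress Thermometer, and the simulation uses a two-group z-test where the plan tests a group-by-time interaction over three time points. That stands for the size of the gain, which is why the less favourable rows are shown. It does not touch the dominance, which needs only valid p values.

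Some stronger readings are tempting but not supported:

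- A reader might infer from the words as applicable that the correction may be skipped, or that the family is miscounted. The article lists "The Mini-Mental Adjustment to Cancer Scale (mini-MAC) score" and then cites cut-offs for two summary scales, which suggests at least five tests. But it does not say that both scales are tested, and the family is detail that may be left to the SAP, which is not shown.
- A reader might infer that correlated outcomes make Bonferroni's loss against Holm largest. Holm does not use the correlation. With four effects of 0.5 SD its gain falls from about 11 points at correlation 0 to about 8 at 0.7. At 0.3 SD it rises, but only from about 3 to 5 points.
- A reader might infer that power is lost on every outcome in every case. The smallest p value still faces 0.05/m, so the first rejection is no easier.
- A reader might want the end-of-treatment results made descriptive to shrink the family. The article plans them as analyses: "Secondary analysis will include the analysis of the primary outcome post-intervention and analysis of the secondary and treatment process outcomes detailed previously post-intervention". Dropping that inference is a debatable trade-off and does not follow from this point.

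**Conclusion.** The point holds as an efficiency improvement of low severity. The article fixes a valid procedure that another one dominates at the same familywise error, on the same data and p values. The dominance is a mathematical fact. Its size rests on assumed effects and correlations: for four outcomes, about 8 to 11 percentage points of average power per outcome if all effects are 0.5 SD, 2 to 3 if two of four are real, 3 to 5 if all are 0.3 SD, and none if only one is real. The sample size and the primary analysis are unaffected.

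**What to change.** In Statistical methods {20a}, or in the SAP before the data are analysed, replace the Bonferroni method by Holm's step-down procedure with a two-sided familywise error of 0.05. Apply it to the group-by-time interaction p values over the family of secondary outcomes defined in the SAP. Leave the planned contrasts at the end of treatment and at 12-week follow-up as they are.

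The cost is one sentence, with no added patients, visits or data. The small downside is that Holm has no matching simultaneous confidence intervals as simple as Bonferroni's. The article plans no such intervals and decides by p value, so little is lost.
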